## 14.7 Sponsor Reporting Obligations

The Sponsor will forward all reportable AEs to the appropriate regulatory authorities and the Investigator according to 21 CFR 312, and any other applicable regulations.

# 15. CLINICAL MANAGEMENT

Guidelines for clinical management and temporary product hold/permanent discontinuation of study product are outlined in this section. In general, the Investigator has the discretion to hold study product temporarily at any time if s/he feels that continued product use would be harmful to the subject or interfere with treatment deemed clinically necessary. Unless otherwise specified below, the Investigator should immediately consult the Council's Medical Monitor for further guidance on resuming study product, continuing the hold temporarily, or progressing to permanent discontinuation of study product. The Investigator will document all temporary product holds and permanent discontinuations on applicable CRFs. AEs that led to premature discontinuation will be reported immediately to the Sponsor using the IRE form.

## 15.1 Grading System

Grading of AEs should follow the DAIDS AE Grading Table, Version 2.0, November 2014. For grading female genital events, please refer to Addendum 1 (Female Genital Table for Use in Microbicide Studies). Tables can be found in Appendix 5. The final determination of the grade will be by the consensus of the PI, the Medical Monitor, and the Medical Safety Director for this study.

## 15.2 Dose Modification Instructions

No dose modifications will be undertaken during this study.

## 15.3 Discontinuation of Study Product in Response to Adverse Events

### 15.3.1 Grade 1 AEs and Unrelated Grade 2 AEs

In general, individual subjects who develop a Grade 1 AE regardless of relatedness, or an unrelated Grade 2 AE may continue use of their assigned study product per protocol, at the Investigator's discretion.

### 15.3.2 Related Grade 2 AEs; Grade 3 and 4 AEs

Individual subjects who develop a related Grade 2 AE, or Grade 3 AE, regardless of relatedness to study drug, will be evaluated by the PI, Medical Monitor and Medical Safety Director for possible discontinuation from the study. Individual subjects who develop a Grade 4 AE, regardless of relatedness to study drug, will be evaluated by the PI, Medical Monitor and Medical Safety Director and discontinued from the study.

### 15.3.3 Halting enrollment

In the circumstance where any of the following criteria are met and confirmed by the PI, the Medical Monitor, and the Medical Safety Director for this study, enrollment in this study will be stopped:

- Two Grade 3 AEs that are similar and attributed to the active study drug;
- Any Grade 4 AE attributed to the active study drug.

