## 7.3 Duration of Treatment

In the OL period, duration of treatment is one day. Each of the seven subjects will receive a single dose of PC-6500. In the randomized period, duration of treatment will be 14 days; each of the subjects will self-administer one of the two assigned study products (PC-6500 or PC-535 [CG placebo]) once daily for 14 consecutive days, with five doses administered under clinical supervision and the remaining nine doses administered at home.

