### ***Main study (randomized period):***

Each subject will have 10 scheduled visits, including screening (see Figure 2). The screening visit (Visit 0) can take place up to 45 days prior to enrollment. Subjects will be enrolled at Visit 1/Enrollment but will not begin dosing until the following week (after biopsies have healed). Dosing begins on Visit 2/Day 1 and lasts 14 days. Once dosing begins, subjects will attend the clinic for: Visit 3/Day 3, Visit 4/Day 8, Visit 5/Day 11, Visit 6/Day 14, Visit 7/Day 15, Visit 8/Day 21 (final safety assessment) and Visit 9/Day 28 (blood draw for ADA testing). Active follow-up from enrollment through study exit will be 35-45 days, depending on the duration of menses. Total study duration will be up to 80-90 days, including screening.

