### 11.2 OL Safety Period, Visit 1: Enrollment/Dosing (Day 1)

Enrollment/Visit 1 should occur as early as possible in the subject's menstrual cycle after menses ends. If more than 30 days elapse between Visit 0/Screening and Visit 1/Enrollment, screening procedures must be repeated. No one may be screened more than twice.

Prior to scheduling Visit 1, the Eligibility Criteria (Sections 8.3 and 8.4) should be reviewed to ensure the subject meets all criteria. Visit 1 is the subject enrollment visit and the sole day of study product use.

| OL Safety Period
Visit 1
(Study Day 1)
PRE-Dose #1       |        |                                                                                                                                                                                                                                                                                                                                                                                                                                                                                                                                                                                                                                                                                                                                                                                                                                                                                                                                       |

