## 15.5 Criteria for Early Termination of Study Participation

Subjects may voluntarily withdraw from the study for any reason at any time. In addition, the Investigator may withdraw subjects from the study for any of the following reasons:

- Indeterminate or positive HIV-1 rapid test
- Acquisition of an STI
- Other medical reasons, including symptomatic vaginal infection diagnosed after enrollment
- Pregnancy
- Report of use of post-exposure prophylaxis (PEP) for HIV exposure
- Report of use of prohibited medications as described in Section 9.8.2
- Subject is unable or unwilling to comply with required study procedures or has failed to follow protocol requirements, including failure to use study product, in a manner judged by the site investigator to be severe enough to affect study outcomes

- Subject might be put at undue risk to their safety and wellbeing by continuing product use, according to the judgment of the Investigator.
- The study Sponsor, government or regulatory authorities, including FDA and Office for Human Research Protections (OHRP), or site IRB terminates the study prior to its planned end date.

Every reasonable effort should be made to complete a final evaluation of subjects who withdraw or are withdrawn from the study prior to completing follow-up. Study staff members will record the reason(s) for all withdrawals in subject's study records.

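### In the randomized period the halting rule stops enrollment but not dosing, so women already enrolled can still start or continue the 14-day course after a confirmed safety signal

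*Protocol*

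**What the plan says.** Section 15.3.3 lists two triggers: two similar Grade 3 adverse events attributed to the active drug, or any Grade 4 event attributed to it. When the PI, the Medical Monitor and the Medical Safety Director confirm either one, "enrollment in this study will be stopped". Dosing is not mentioned.

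In the randomized period, enrollment and dosing are separate steps. Section 7.4 states: "Subjects will be enrolled at Visit 1/Enrollment but will not begin dosing until the following week (after biopsies have healed"). Section 7.5 puts the gap at 7 days or more. Fourteen daily doses follow, "with five doses administered under clinical supervision and the remaining nine doses administered at home" (7.3). In the open-label period the two steps coincide: "Visit 1 is the subject enrollment visit and the sole day of study product use" (11.2).

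The other provisions that can stop product are these:

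- **15.3.2** concerns the woman who had the event: "Individual subjects who develop a Grade 4 AE, regardless of relatedness to study drug, will be evaluated" and discontinued. A related Grade 2 or any Grade 3 event leads to evaluation for possible discontinuation.
- **Opening of Section 15:** "the Investigator has the discretion to hold study product temporarily at any time if s/he feels that continued product use would be harmful", with consultation of the Medical Monitor.
- **15.5** lets the Investigator withdraw a woman on grounds that include "Subject might be put at undue risk to their safety and wellbeing by continuing product use, according to the judgment of the Investigator". It also covers termination of the study by the sponsor, the authorities or the IRB.
- **15.7** stops product in a woman who becomes pregnant.
- **7.7** is a single go/no-go decision before the randomized period opens.

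**The concern.** A halting rule fixes in advance what happens once its own criteria are met. Here the criteria concern harm from the drug, but the consequence is attached to a step that comes before exposure. A woman who passed Visit 1 the day before the trigger has had no gel. Followed to the letter, the rule lets her go on to a full course.

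This is the first trial of griffithsin in humans, and the randomized period is the first repeated exposure. The subjects are healthy and expect no direct benefit, so nothing therapeutic favours continued dosing during a review. Nine of the 14 doses are taken at home, so a decision to hold also depends on someone reaching the woman, and 15.3.3 does not require that contact.

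**Working it through.** The protocol gives no figure for this point, so there is none to reproduce. The check has a text part and a size part.

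**Text.** Does any provision stop dosing in *other* enrolled women when a 15.3.3 trigger is confirmed?

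- 15.3.2 and 15.7: no. They act on the affected woman only.
- Opening of Section 15 and 15.5: they permit a stop by judgment or by a sponsor, authority or IRB decision, but neither is linked to the triggers.
- 7.7: no. It is spent before the randomized period begins.

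In the open-label period, stopping enrollment also stops dosing. The gap is therefore confined to the randomized period.

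**Window from Visit 1 to Dose 14.** The cycle-day windows come from 7.5 and Appendix 2; a 28-day cycle is assumed.

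- Not on hormonal contraception, Visit 1 to Visit 2: cycle Day 28 to Day 7 = 7 days; Day 21 to Day 10 = 17 days.
- On hormonal contraception: Day 22 to Day 1 = 7 days; Day 15 to Day 4 = 17 days.
- Dose 14 is 13 days after Dose 1, so the window is 7 + 13 = 20 to 17 + 13 = 30 days.

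Cross-check with 7.4: "Active follow-up from enrollment through study exit will be 35-45 days, depending on the duration of menses". Exit is Day 28, which is 14 days after Dose 14. That gives 35 − 14 = 21 to 45 − 14 = 31 days, which agrees to within a day.

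**Women in the window at a random stop** = monthly enrollment × window ÷ 30.4. The rates are assumptions; 2 a month is 20 women over the full 10 months in 7.2.

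| Enrollments per month | 20-day window | 30-day window |
|---|---|---|
| 0.5 | 0.33 | 0.49 |
| 1 | 0.66 | 0.99 |
| 2 | 1.32 | 1.97 |
| 3 | 1.97 | 2.96 |

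With the planned 7:3 allocation, 2 a month gives 0.7 × 1.32 = 0.92 to 0.7 × 1.97 = 1.38 women on PC-6500.

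**Scheduled doses left per woman in the window** = (gap × 14 + sum of 1 to 13) ÷ window, where the sum is 91.

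- Short gap: (7 × 14 + 91) ÷ 20 = 189 ÷ 20 = 9.45.
- Long gap: (17 × 14 + 91) ÷ 30 = 329 ÷ 30 = 10.97.

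The full 14 remain only if she has not started: 7 ÷ 20 = 35% to 17 ÷ 30 = 57% of the window. At 4 mg per applicator (9.11), that is up to 14 × 4 = 56 mg of griffithsin if she is on active gel.

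**Home doses.** Clinic doses are numbers 1, 3, 8, 11 and 14 (9.3.2). The home runs between them are 1 + 4 + 2 + 2 = 9 doses, the longest being Days 4 to 7.

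**The case against.** The best reply is that 15.3.3 does what its title says, and that dosing decisions sit elsewhere in Section 15. The people who confirm a trigger include the PI and the Medical Monitor, who decide on product holds, and the sponsor can end the study. Harm requires them to confirm a drug-attributed Grade 4 event, or two similar Grade 3 events, and then let dosing go on. Practical controls also limit exposure. Dose 1 and four later doses are taken in the clinic under supervision, applicators are supplied visit by visit, and the longest home run is four doses. So the average of 9.5 to 11 doses left counts scheduled doses, most of which need staff to act.

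Much of this stands as a limit on size. The hold powers are real, and the team would probably use them. Without further staff action, a woman has at most about four scheduled home doses before her next clinic visit. The numbers also rest on assumed accrual: the 10 months cover both study periods, while 9.4 reports slow accrual and says 20 women will not be reached. Because 9.4 also moves the remaining women to case-by-case assignment, the 70% active share is approximate. All the figures are conditional on a trigger, whose probability is not estimated.

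It does not close the gap. The hold and withdrawal powers are discretionary, and staff who follow the protocol as written would give the clinic doses and hand out the next supply. The site manual, which is not at hand, may describe how to contact women, but the consequence of a halting rule belongs in the rule.

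**Conclusion.** The point holds for the randomized period, with high confidence in the reading of the text. After a confirmed 15.3.3 trigger, no provision mandates that first or further doses stop in the other women already enrolled. The number affected at one time is small: about 1.3 to 2.0 women at 2 enrollments a month, and 0.3 to 3.0 over the assumed range of 0.5 to 3, with the lower part more likely. These counts assume steady accrual and a 28-day cycle. This does not mean that dosing must continue; it means that the decision is left to case-by-case judgment just when the protocol's own criteria have been met. It should be fixed, because this is a first-in-human trial in healthy women and the remedy is cheap.

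**What to change.** Amend 15.3.3 so that, when either criterion is confirmed:

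- enrollment stops, and all first and further doses in enrolled women, including home doses, are suspended;
- the suspension lasts until the PI, the Medical Monitor and the Medical Safety Director complete a safety review and decide whether to resume or terminate;
- the site at once contacts every woman holding applicators and documents the hold on the CRF.

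The cost is a short amendment and a matching site procedure, with no extra visits or subjects. If the rule is triggered, about 1 to 3 women, fewer with slow accrual, may have incomplete 14-day courses and incomplete Day 14 PK.

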## 15.4 Management of Specific Toxicities

There are no known specific toxicities of GRFT, but because it is a mannose binding lectin, mannose could be an antidote for unexpected toxicity.

## 15.5 Criteria for Early Termination of Study Participation

Subjects may voluntarily withdraw from the study for any reason at any time. In addition, the Investigator may withdraw subjects from the study for any of the following reasons:

- Indeterminate or positive HIV-1 rapid test
- Acquisition of an STI
- Other medical reasons, including symptomatic vaginal infection diagnosed after enrollment
- Pregnancy
- Report of use of post-exposure prophylaxis (PEP) for HIV exposure
- Report of use of prohibited medications as described in Section 9.8.2
- Subject is unable or unwilling to comply with required study procedures or has failed to follow protocol requirements, including failure to use study product, in a manner judged by the site investigator to be severe enough to affect study outcomes

- Subject might be put at undue risk to their safety and wellbeing by continuing product use, according to the judgment of the Investigator.
- The study Sponsor, government or regulatory authorities, including FDA and Office for Human Research Protections (OHRP), or site IRB terminates the study prior to its planned end date.

Every reasonable effort should be made to complete a final evaluation of subjects who withdraw or are withdrawn from the study prior to completing follow-up. Study staff members will record the reason(s) for all withdrawals in subject's study records.

### **15.6 Subject Withdrawal**

Subjects withdrawing from the study will not be replaced. Safety data will be included in the analysis from any subjects who withdraw. All efforts should be made to contact any subject who decides to withdraw from the trial. All final safety evaluations should be performed. The main reason for discontinuation prior to completing follow up will be recorded. If a subject discontinues due to an AE, the reasons must be submitted on the IRE forms for SAEs and AE leading to discontinuation. The Council's Study Manager will be informed with respect to enrollment and withdrawals from the study.

### **15.7 Pregnancy and Pregnancy Outcome**

Pregnant women are excluded from this study. If a subject becomes pregnant at any time during the course of the study, she will discontinue study product use immediately and will be terminated from the study. The subject will be followed beyond the last study visit until the outcome of her pregnancy. Pregnancy-related data will be collected using a pregnancy CRF for any pregnancy detected during the study. Follow-up for pregnancy outcome, birth defect or major anomaly outcome, and any associated AE/SAE will be reported on the CRFs and to the Council.

Pregnancy testing will be performed at weekly study visits and subjects will be encouraged to report all signs or symptoms of pregnancy to study staff. The Investigator will counsel any subject who becomes pregnant regarding possible risks to the fetus according to site SOPs.

## **16. QUALITY CONTROL AND ASSURANCE**

The study will be conducted in accordance with ICH Good Clinical Practice (GCP) and the SOPs of the Population Council and the study site.

The Council will conduct a site initiation visit prior to initiation of data collection.

During the conduct of the trial, the Council or its designees will conduct periodic monitoring visits to ensure that the protocol and GCPs are being followed. The monitors may review source documents to confirm that the data recorded on CRFs is accurate. The Investigator and institution will allow the Council's monitors or its designees and appropriate regulatory authorities direct access to source documents to perform this verification.

The trial site may be party to review by the Population Council or local IRB and/or to quality assurance audits performed by the Council and/or its designees, and to inspection by appropriate regulatory authorities. It is important that the Investigator(s) and their relevant personnel are

available during monitoring visits and possible audits or inspections, and that sufficient time is devoted to the process.

The study products (PC-6500 and PC-535) will be manufactured at the Population Council's Center for Biomedical Research (CBR) in a lab certified in accordance with current Good Manufacturing Practices (GMP).

## 17. STATISTICAL METHODS

### 17.1 Overview and Summary of Design

This is a Phase 1 single-site, double-blind, parallel-group, randomized, placebo-controlled trial, preceded by an OL active treatment safety run-in period. Subjects in the OL period (n=7) will receive only one dose of gel, administered in the clinic. The main, randomized period of the study will enroll up to 20 subjects dosing once per day for 14 consecutive days with a mix of in-clinic and at-home dosing. Product randomization will be approximately 7:3 (PC-6500:PC-535) and subjects will also be randomized (approximately 1:1) to one of two time points for CVL specimen collection after the first dose. Details will be described in a statistical analysis plan (SAP).

### 17.2 General Considerations

In general, descriptive statistics will be presented for demographic and baseline characteristics and for each of the endpoints for each treatment group and for the two treatment groups combined. Point estimates and corresponding 2-sided 95% confidence intervals will be presented for endpoints, where appropriate.

### 17.3 Determination of Sample Size

No formal sample size calculations were carried out for this study. A sample size of 20 subjects (14 active), allowing for a 10% drop out rate, is considered sufficient to evaluate the safety of PC-6500 and to assess the PK of GRFT.

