## 2. PROTOCOL SYNOPSIS

**Study Title:** A Phase 1 Trial to Evaluate the Safety, Pharmacokinetics (PK) and Pharmacodynamics (PD) of PC-6500 (Griffithsin [GRFT] in a Carrageenan [CG] Gel) in Healthy Women

**Short Title:** Safety, PK and PD of GRFT for vaginal use

**Clinical Phase:** Phase 1

**IND Sponsor:** Population Council, Inc.

**Protocol Chair:** [name]

**Sample Size:** 27 female subjects (7 in open-label single-dose period; 20 in randomized, double-blind multiple-dose period)

**Study Population:** Healthy HIV-seronegative women aged 18-49 who are sexually abstinent during the study

**Study Site:** One US site, Albert Einstein College of Medicine (Einstein), Bronx, NY

**Study Duration:** Approximately 8 days of active participation per subject in the open label (OL) period (n=7) and 45 days of active participation per subject in the randomized, placebo-controlled, double-blind period (n=20); approximately 10 months for overall accrual.

**Study Design:** In the OL safety run-in period, 7 (seven) women will receive a single 4 g dose of PC-6500 (GRFT in a CG gel) with PK assessments through 12h and a final assessment on the following day at 24h, a PD assessment 24h post-dose; and a final safety assessment one week later (Day 8). After the first 7 women have received the single dose of PC-6500 gel and all safety/PK/PD assessments have been completed, there will be a pause in recruitment while data are reviewed. Data from the OL period will inform the subsequent PK and PD assessments in the main, randomized period of the study.

The main study will enroll 20 new subjects in a randomized, placebo-controlled, double-blind design to assess safety, PK and PD of 4 g PC-6500 used once daily for 14 consecutive days. Subjects in the main study will be randomized to PC-6500 gel (n=14) or PC-535 (CG placebo) gel (n=6). Subjects will also be randomized to one of two time points (4 hours or 8 hours) for blood and cervicovaginal lavage (CVL) specimen collection after Dose 1. At baseline (at least 7 days before Dose 1) and after Dose 14, biopsies, CVLs, and vaginal swabs will be collected to quantify concentrations of GRFT and CG (CVL); to measure antiviral activity in cell-based

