### 9.4 Method of Assigning Study Subjects to Study Intervention Groups

All subjects will be sequentially assigned to the next available unique identification (ID) number upon signing the informed consent form, prior to undergoing any screening procedures. For the single-dose OL period of the study, all subjects will receive PC-6500 (i.e. this period will not be blinded) and their ID number (PTID) will be their only ID number. For the main, randomized study period, each subject will receive a PTID at screening. At the outset of the trial, participants have been sequentially assigned to the next available randomization number after confirmation of eligibility at the enrollment visit (Visit 1). However, due to slower than anticipated accrual, it will not be feasible to enroll all 20 women. For the remaining participants who enroll, the Population Council Senior Statistician will assign the kit number and time point assignment, on a case by case basis, to balance the number of women assigned to product vs placebo; and to maintain the balance in post-dose specimen collection time points. Clinic staff will document the randomization number assignments which will determine which kit is given to the subject. The women in the main, randomized study period will be randomly assigned to either PC-6500 (n=up to 14) or PC-535 placebo gel (n=up to 6).

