## 9.5 Randomization

A statistician who is not associated with the trial will create the randomization scheme which will pre-assign subjects to study intervention group. All subjects in the main study will also be stratified (1:1) for PK blood sampling and CVL collection to 4h (n=up to 10) or 8h (n=up to 10) post-Dose 1. Randomization occurred in blocks of ten (10). Each block of 10 was to include 3 placebo assignments and 7 active assignments; however, the final tally of active versus placebo will be unknown until the end of the study. Each block of 10 also includes 5 assignments to PK/CVL collection at 4h and 5 assignments to PK/CVL collection at 8h as indicated in the table below.

| Intervention/Specimen Collection Time Stratification | Active | Placebo | Total |
|------------------------------------------------------|--------|---------|-------|
| 4h post-Dose 1                                       | n=7    | n=3     | n=10  |
| 8h post-Dose 1                                       | n=7    | n=3     | n=10  |
| Total                                                | n=14   | n=6     | N=20  |

Applicators will be packaged in kits which will be numbered 1-20 for the main study. The first subject randomized will receive applicators from kit number 1. The second subject will receive applicators from kit number 2, and so on. If a subject needs replacement applicators, the site will contact the Population Council team to be told which back-up applicator numbers should be given to the subject, based on the subject's randomization number. Study staff will receive with a list of kit numbers and specimen time point randomization assignments for all 20 participants. The randomization numbers will not identify PC-6500 or PC-535. The specimen time points will not be blinded – i.e. study staff will know which subjects will be scheduled for 4h and 8h time points when they receive the list from the Population Council.

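### Section 17.3 rests its sample-size statement on 20 randomized women (14 active), a total that section 9.4 says cannot be enrolled; the expected number per arm is not given

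*Protocol*

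**What the plan says.** Section 17.3 of the protocol opens with "No formal sample size calculations were carried out for this study" and continues: "A sample size of 20 subjects (14 active), allowing for a 10% drop out rate, is considered sufficient to evaluate the safety of PC-6500" and, in the same sentence, to assess the PK of GRFT. No event rate, precision target or power accompanies this.

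Section 9.4 reports slow accrual and concludes that "due to slower than anticipated accrual, it will not be feasible to enroll all 20 women". It gives the arms as at most 14 and at most 6, and hands the remaining assignments to the sponsor's senior statistician case by case. Section 9.5 adds that "the final tally of active versus placebo will be unknown until the end of the study".

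Other places fall on either side:
- Upper-bound wording: sections 8.1, 9.4 and 17.1, the arm-size cells of the synopsis allocation table, and the time-point numbers in the text of 9.5.
- Full size kept: the synopsis text ("The main study will enroll 20 new subjects in a randomized, placebo-controlled, double-blind design", followed by fixed arms of 14 and 6), section 17.8 (10 women at each post-Dose 1 CVL time point) and the title of Appendix 2 (n=20).
- Mixed: the 9.5 table shows 14 and 6, but the text around it describes the block scheme partly in the past tense and leaves the final split open.

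On withdrawals, 15.6 says "Subjects withdrawing from the study will not be replaced" and keeps the safety data of women who withdraw. Section 17.4 defines the safety population as every woman who inserted at least one dose.

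**The concern.** Because no formal calculation was made, the sentence in 17.3 is the whole justification of the trial's size for its two primary objectives, safety and PK. It names a total that 9.4 says will not be reached. The protocol gives no expected total, no minimum total, and no view on whether a smaller trial still serves those objectives.

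At stake is how a clean safety result may be read. Zero events in a smaller active arm exclude less than zero events in 14. A reader who takes 17.3 at its word would attach the wrong denominator to that result. The same holds for the comparison with placebo if the placebo arm is the one that shrinks.

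**Working it through.** **1. The plan's own figures.** Inputs: 20 subjects, 14 active and 10% dropout (17.3); allocation about 7:3 (17.1).
- 20 × 0.7 = 14 active; 20 × 0.3 = 6 placebo.
- 20 × 0.9 = 18 completers; 14 × 0.9 = 12.6 active completers.

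These agree with one another, so 17.3 contains no arithmetic error.

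**2. What a total below 20 implies.** Since 14 + 6 = 20, any total of 19 or fewer leaves at least one arm short. At 19, for example, the arms could be 14 and 5, or 13 and 6. Likewise 10 + 10 = 20, so the two CVL groups in 17.8 cannot both have 10.

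**3. Scale of the effect on the active arm.** Section 17.2 plans two-sided 95% intervals where appropriate, so I use that level. For zero events in n women the exact upper limit is 1 − 0.025^(1/n). The chance of at least one case at a true rate of 10% is 1 − 0.9^n. The 10% rate is chosen for illustration and is not in the protocol. The achievable n is not given, so 8 to 14 is an assumed range. At 7:3, a total of 14 gives 9.8, about 10 active, and a total of 12 gives 8.4, about 8.

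| Active women | Upper limit, 0 events | Chance of ≥1 case at 10% |
|---|---|---|
| 14 | 23.2% | 77.1% |
| 10 | 30.8% | 65.1% |
| 8 | 36.9% | 57.0% |

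**4. If the shortfall falls on placebo instead.** The active figures stay at 23.2% and 77.1%. The zero-event upper limit on placebo moves from 1 − 0.025^(1/6) = 45.9% with 6 women to 1 − 0.025^(1/5) = 52.2% with 5.

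**5. Dropout.** A woman who withdraws after her first dose stays in the safety population (17.4) and her safety data are analysed (15.6). The 12.6 from step 1 is therefore not a safety denominator. It bears on Day 14 PK and on the number completing 14 days. Only a woman lost between enrollment and Dose 1 leaves the safety count.

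**The case against.** The strongest reply is that nothing promised is lost. Section 17.3 disclaims a calculation and states no precision, so there is no stated precision to fall short of, and the limits above are derived by the reader from n. Calling 20 sufficient does not say that fewer is insufficient. The "allowing for a 10% drop out rate" wording shows that 18 completers were acceptable, so a shortfall of one or two with no dropout would stay within that number. All of this stands. It does not rescue the sentence, because the allowance is for dropout among 20 enrolled, and nothing says that the shortfall is only one or two.

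A reader might infer that the active arm will fall below 14. The documents do not show this. Section 9.4 rules out 20 in total, not 14 active, and with case-by-case assignment the shortfall could fall wholly on placebo. Section 17.1 still gives about 7:3, while 9.4 speaks of balancing product against placebo, so the text does not settle which arm gives way.

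A reader might also take 10% off the safety denominator, because withdrawals are not replaced. Sections 15.6 and 17.4 exclude that reading for any woman who has been dosed.

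The seven open-label women also receive PC-6500, so single-dose exposure can reach 14 + 7 = 21, with a zero-event upper limit of 1 − 0.025^(1/21) = 16.1%. That is fair for single-dose safety. These women have one dose and may not enter the randomized period, so they add nothing on 14-day use.

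Finally, the 9.5 table is qualified by the text around it and can be read as the original list. It needs a label more than a correction.

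**Conclusion.** The point holds as an internal inconsistency between two current statements: 17.3 justifies a size of 20 (14 active) that 9.4 says will not be enrolled. The synopsis text, 17.8 and Appendix 2 repeat the full size. At least one arm will be smaller than the one called sufficient, and that follows from addition alone.

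The size of the loss cannot be computed, because neither the achievable total nor its split is stated. If the active arm ended at 10 or 8, the zero-event upper limit would rise from 23% to 31% or 37%, and the chance of seeing a 10% event would fall from 77% to 65% or 57%. Those figures rest on the assumed range of 8 to 14 active and concern 14-day exposure only.

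The documents do not support calling this a calculation error, a breach of a stated precision, or proof that the trial has become too small. No endpoint or analysis method changes.

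**What to change.** - In 17.3, give 20, 14 and 6 as upper bounds, and add the expected or minimum number per arm now foreseen.
- Replace the sufficiency statement with what that number supports for 14-day exposure. The zero-event upper limit and the chance of seeing a 10% event are one compact way to say it.
- Do not reduce the safety denominator by the 10% dropout. Mention dropout for Day 14 PK and for completers.
- Align the synopsis text, the time-point numbers in 17.8 and the title of Appendix 2 with the upper-bound wording of 8.1, 9.4 and 17.1, and label the 9.5 table as the original scheme.
- Do not add participants.

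The cost is one rewritten paragraph and a few wording changes in an amendment. The protocol would then state openly what a smaller trial can exclude, which will look less reassuring than the present sentence if the active arm ends below 14.
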